## **7.5. Follow up**

As part of this research, follow-up mostly concerns adolescents vaccinated in the middle schools. After the vaccine injection, each adolescent will stay with the doctor and nurse of the vaccination center for 15 - 20 minutes to check that they do not develop any adverse reactions. Beyond this duration, if an adverse effect occurs, the adolescent concerned notifies the school nurse (or the middle school research referent if it is not the school nurse) who is responsible for transmitting the information to the PrevHPV SC, which notifies the regional pharmacovigilance center of the region where the middle school is located.

The follow-up also covers participants in the KABP-6C survey, interviewed twice (T0 and T1). Students, parents of students and GPs agreeing to respond to the KABP-6C surveys will be asked to complete a standardized self-administered questionnaire twice, at T0 before the interventions and at T1 after the interventions.

There is no 'exit study visit' strictly speaking as part of this research.

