### **7.2. Inclusion, information, and participation agreement**

The selection process, information - participation agreement, and inclusion is as follows (see paragraph 5.3 Selection methods):

- Identification of eligible academies,
- Information from the rectorates of eligible academies and diocesan directorates of eligible departments by mail (DGESCO director letter + PrevHPV's SC letter),
- Identification of 409 eligible municipalities in eligible academies,
- Information by mail then telephone from the principals and directors of the middle schools of the 409 municipalities + request for participation agreement (→ identification of the 90 participating municipalities),
- Randomization of the allocation group (group 1 to 6) of the components for each participating municipality,
- Information for principals and directors of each middle school in their assigned group,
- Information for the mayors of each of the 90 participating municipalities and the corresponding

departmental councils,

- Information for GPs in municipalities in groups 1, 2 and 5, verification of eligibility and agreement to participate in training.

For each middle school of the 60 municipalities randomized to groups 1, 2, 3 and 4 (benefiting from EMM alone or EMM + facilitation of access to vaccination), the principal/director is in charge of informing the staff (health, teaching, administrative) of his middle school of the component they will receive. It will be essential that a referent be appointed within each middle school (school nurse/doctor, biology teacher, administrator, etc.) to be the main contact for the PrevHPV SC and to act as a link between the research teams and the actors in the field of experimentation.

Students and parents (or legal guardians) of each middle school in the 60 municipalities are informed by a letter at the end of 2020 by the referent and the principal/director of the component(s) (EMM or EMM + facilitation of access to the vaccination) deployed in their middle school between January and May 2021.

For the middle schools of the 30 municipalities randomized to groups 1 and 3 (benefiting from the 'Facilitation of access to vaccination' component), an information letter and collection of consent to vaccination are sent by the referent and/or each principal/school director, in January/February 2021, to the parental authority of each student enrolled in the school to propose the initiation of HPV vaccination at their child's school.

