1179 organization of each establishment.
- 1180 (vii) The doctor of the vaccination center verifies that the adolescent meets the inclusion criteria of the  
1181 protocol, vaccinates and completes the health record.
- 1182 (viii) On the nominative list of consents to vaccination, the vaccination center nurse or the PrevHPV  
1183 project manager records whether the vaccination is carried out or not on a paper list.
- 1184 (ix) All students who have received an injection remain under the supervision of the vaccination center  
1185 doctor for 15 to 20 minutes before returning to class. During the post-vaccination surveillance period,  
1186 a satisfaction questionnaire is given to adolescents who complete it on site. The nurse gives the  
1187 student a post-vaccination letter in a sealed envelope intended for his or her parents in which it will  
1188 be mentioned whether or not the vaccination has been carried out and the future injection(s) to be  
1189 planned. (for parents who have consented but whose adolescent has not been vaccinated, a non-  
1190 vaccination letter is sent to them). Subject to the acceptance of the parents of the vaccinated child  
1191 (information formalized in the vaccination consents), a letter addressed to the adolescent's treating  
1192 physician is sent directly either by the vaccination center or by the PrevHPV project manager of the  
1193 geographical area concerned. In addition, parents can give a note to their community pharmacist if  
1194 they wish to complete the pharmaceutical file.

In the post-vaccination information letters to parents and treating doctors, it will be specified that a second or even a third injection is necessary for the vaccination to be complete as well as the period at which it should be carried out. The prescription for the following injection will be made by the doctor at the vaccination center and provided with the other documents for parents.

At the end of the vaccination day, the satisfaction survey will be made available to the professionals of the school involved in the intervention in order to measure the possible incidence during the adolescents' school hours. The completed satisfaction questionnaires will be collected by the middle school referent.

Overall assessment of the vaccination day:

- Number of days organized
- Number of vaccinations requested
- Number of complete vaccination consents,
- Number of incomplete vaccination consents
- Number of vaccinations carried out

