## **9.2. Responsibilities of the investigator**

The investigator immediately declares to the sponsor any serious adverse effect likely to be linked to the research procedures and any new fact, that is to say any new safety data which may lead to a reassessment of the benefit/risk ratio of research, or which might be sufficient to consider changes to the research documents.

To do this, he must immediately send a copy of the document detailing the circumstances of the serious adverse effect or the new fact to the [[contact]](mailto:[contact])

Any other adverse effect likely to be linked to a product taken by the participant must be declared by the investigator to the competent structures in accordance with the applicable regulations (<http://social-sante.gouv.fr/grands-dossiers/signalement-sante-gouv-fr> in France).

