### **15.1. Steering Committee (SC)**

This operational committee is made up of the Scientific Managers of each party and a representative of the sponsor. It meets monthly to develop, implement and monitor the progress of the research.

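### After the 15-20 minute observation, the protocol's only stated adverse-effect route starts with the adolescent telling someone at school; parents and physicians are not on it, so reactions away from school may be reported late or not at all.

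*Protocol*

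**What the plan says.** Section 7.5 describes two stages for pupils vaccinated at school.

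- **Direct observation.** "each adolescent will stay with the doctor and nurse of the vaccination center for 15 - 20 minutes".
- **Afterwards.** "Beyond this duration, if an adverse effect occurs, the adolescent concerned notifies the school nurse". Where the nurse does not hold the referent role, the school's referent is the alternative recipient. Whoever receives the report passes it to the Steering Committee, and the committee alerts the regional pharmacovigilance centre. The section closes: "There is no 'exit study visit' strictly speaking as part of this research".

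Section 7.2 lists who may act as referent: "school nurse/doctor, biology teacher, administrator, etc".

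Section 9.2 sets the onward duty: "The investigator immediately declares to the sponsor any serious adverse effect likely to be linked to the research procedures". Other product-linked effects go to the competent national structures.

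Section 8, step (ix) of the facilitation component, sends parents a letter after the vaccination session and, if they accept, sends one to the treating physician. The described content is whether the injection was given and what remains to be done: "In the post-vaccination information letters to parents and treating doctors, it will be specified that a second or even a third injection is necessary".

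**The concern.** The first link in the chain is a child, usually aged 11 to 14, and the recipient is at school. The people most likely to know of a reaction that evening, over a weekend or in a hospital are the parents and the physician, and neither is named as a reporter. The vaccination-centre doctor, who leaves after the session, is not named as a recipient either.

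Two things are at stake. The immediate duty in section 9.2 can only be met if the investigator hears of the event, and the sole described feed is untimed and may pass through someone without clinical training. Also, the route works best for a pupil who is well enough to be in class, so ascertainment is weakest where a prompt report matters most.

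**Working it through.** The protocol gives no figure to reproduce here. The check is a comparison of the sections, with a short calculation for scale.

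**Is there another route into the trial after the observation period?**

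1. *Section 7.5:* pupil to nurse or referent, to Steering Committee, to pharmacovigilance centre. No parent, physician or vaccination-centre report, no scheduled safety contact and no exit visit.
2. *Section 9.2:* says what the investigator forwards and to whom. It starts once the investigator already knows.
3. *Section 8, step (ix):* the letters are described as covering vaccination status and further injections. No reporting request is mentioned.
4. *Section 8, step (x):* a wrap-up meeting with the referent and the head of the school in the following weeks. No safety enquiry is specified.
5. *Section 8, step (xi):* later reminders to parents and physicians concern completing the schedule.
6. *Section 10.1:* no individual health data are collected beyond vaccination status.
7. *Section 16.2:* no monitoring plan is foreseen.

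So section 7.5 is the only described entry point, and nothing else acts as a backstop.

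**Where in the chain is the weakness?** Mainly at the start. The Steering Committee includes the sponsor's representative (section 15.1) and the coordinating investigator (section 1.1), so a report that reaches the committee has reached the people bound by section 9.2. What is missing is a dependable way for the report to start, and a named person and time limit for passing it on.

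**Do the risk statements agree?** Section 9.3 calls the added risk negligible with reference to self-administered questionnaires. Section 14.2 names the vaccine injection as the only research-related risk. These need reconciling, because the second makes ascertainment after injection relevant and the first does not mention it.

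**Scale.** Inputs: 30 municipalities in groups 1 and 3 (section 4.2); 466 pupils per school and one school per municipality (section 11.2); 1.7 anaphylaxis cases per million doses (sections 1 and 14.2). School uptake is not given, so 5% to 20% is my assumption.

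- Pupils: 30 x 466 = 13,980.
- Doses: 13,980 x 0.05 = 699; 13,980 x 0.20 = 2,796.
- Expected anaphylaxis: 699 x 1.7/1,000,000 = 0.001; 2,796 x 1.7/1,000,000 = 0.005.
- Upper 95% bound if no event of a given kind is reported (3/n): 3/699 = 0.43%; 3/2,796 = 0.11%. These bounds hold only if every event is captured, which the section 7.5 route does not ensure.

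**The case against.** The strongest reply is that this is not a safety trial. The vaccine is authorised for this population and is not itself under study (section 8.1). Safety is neither an objective nor an outcome, and the expected number of serious reactions is close to zero. Section 9.2 also covers non-serious product-linked effects and is not limited to events that come through the school. Nothing forbids a parent from calling the nurse, and section 7.5 sets no deadline, so a pupil can report on return. The full letters are not shown and may already carry a reporting instruction.

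Much of this stands, and it limits the point. Several stronger readings are tempting but are not supported:

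- *That an absent pupil cannot report at all, or that severe reactions are shown to be the ones most often missed.* Late reporting remains possible, and the documents give no rate by severity. Mild reactions may also go unmentioned.
- *That a committee which meets monthly imposes a delay of up to a month.* Section 15.1 says "It meets monthly to develop, implement and monitor the progress of the research", but section 7.5 does not make notification wait for a meeting, and project managers are in contact with the schools.
- *That the adverse-effect count in section 8 would be biased low.* That count belongs to the assessment of the vaccination day, when pupils are under observation. The protocol does not make it a criterion for extending the component.
- *That school opening hours measure the chance of a report.* A report need not be made at the moment of onset.

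The reply does not remove the core. Section 9.2 presupposes knowledge of the event. A physician's report to national pharmacovigilance is not said to reach the trial. Whatever the letters contain, section 7.5 itself defines the route without parents or physicians.

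**Conclusion.** The point holds as a weakness in how reactions after the observation period are ascertained. Section 7.5 fixes one pupil-initiated route and leaves out the adults best placed to report. Reactions that keep a pupil at home or in hospital are therefore less likely to reach the trial, or may reach it late, and the immediate duty in section 9.2 has no reliable feed.

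The size is small in expected events: about 700 to 2,800 first doses under the assumed uptake, with far fewer than one anaphylaxis case expected. The loss of reports cannot be quantified from the documents; the direction is inferred from the route itself. The vaccination-coverage outcome and its analysis are not affected. The change should be made, but the trial's main conclusions do not depend on it. The part about the letters is conditional on the full letters not already containing a reporting instruction.

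**What to change.** 1. Amend section 7.5 and section 8, step (ix), so that parents and the treating physician may report an adverse effect directly to the trial. Keep the school nurse as an additional route.
2. Print a trial safety contact and a short reaction-report line in the existing post-vaccination letters, if they do not already have one.
3. Have reports go without delay to a designated clinician within the existing teams, who triggers the section 9.2 declaration.
4. Reconcile section 10.1, which limits individual health data to vaccination status, with the receipt of such reports. Reconcile section 9.3 with section 14.2 on whether the injection is a research risk.

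I would not rely on the 6-month reminder to ask about reactions. Recall at that distance is weak, and six months after a spring 2021 vaccination falls after the April-May 2021 end of research in section 7.8.1.

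The cost is an amended paragraph, a few lines in letters already planned, the designation of a clinician, and some additional non-serious reports to triage. Aligning the data description in section 10.1 may need attention in the data-protection authorisation that section 14.6 requires.

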## **7.6. Expected duration of participation**

- Duration of participation of GPs: 10 months
- Duration of participation in middle schools (adolescents, parents, National Education professionals, SeSa Students): 10 months
- Total duration of the research: 10 months

**(2020-2021 school year)**

## **7.7. Stopping one's participation in the research**

The cessation of participation of a person in the various components proposed as part of this research concerns:

- Adolescents whose holders of parental authority accept vaccination on the middle school site:
  - ✓ Holders of parental authority may withdraw their consent to vaccinate their child(ren), without justification, at any time between the transmission of the latter and the time of injection of the vaccine,
  - ✓ The doctor of the vaccination center may decide not to vaccinate the adolescent if he or she does not meet the inclusion/non-inclusion criteria which are re-checked at the time of injection of the vaccine, or if he or she considers that there is a particular risk for the adolescent.
- Parents of adolescents who agree to participate in the parent information meetings planned as part of the 'EMM' component may change their mind at any time between the date of acceptance and the time the dedicated meeting(s) is held.
- GPs who agree to participate in motivational interviewing training and the use of the decision-aid tool may change their mind at any time between the date of acceptance and the training.
- Participants in the KABP-6C longitudinal survey may stop and/or cancel their participation at any time.

The participation agreement of parents and GPs is an informal agreement, without signed consent as defined in article L. 1122-1-1 of the Public Health Code. This agreement may be withdrawn at any time before their participation (respectively in meetings and training). The only consent collected as part of this study is the consent of adolescents and their parents (holders of parental authority) to be vaccinated (see explanations in part 13.3).

## **7.8. End of research**

### **7.8.1. Definition of end of research**

The end of the research corresponds to the end of the completion of the KABP-6C questionnaires by adolescents, parents and GPs in the 90 participating municipalities (April-May 2021).

### **7.8.2. Description of the rules for permanently or temporarily stopping part or all of the research**

In accordance with article R1123-26 of the Public Health Code, if the interventions have not started within two years following obtaining the favorable opinion of the CPP, the agreement of the committee will be considered lapsed and the research will have to be resubmitted to the authorities to be extended. This extension request must be accompanied by a letter justifying the delay compared to the initial forecast schedule.

During the research, if the defined research timetable is not respected, Inserm may decide to stop it if no other solution can be considered.

The sponsor and the competent authorities may interrupt the research for any other justified reason (major deviations from the protocol which do not guarantee the safety of participants, the quality of the data and the results of the research).

## **8. INTERVENTIONS EVALUATED IN THIS PROTOCOL**

The three components of the intervention were developed: (i) based on a literature review carried out by the PrevHPV SC, (ii) as part of a co-construction process with the different stakeholders, and (iii) in light of the results of the diagnostic phase.

To date, the literature review has been carried out and the co-construction process is being finalized.

The three components are defined but may be refined/slightly modified depending on the results of the diagnostic phase. To date, they are as follows:

- **Education, Motivation, Mobilization (EMM)**

This component targets the parents of all adolescents enrolled in middle school and adolescents enrolled in Grades 8 & 9. It aims to provide scientifically reliable information on HPV infection and its vaccine. To do this, the promotion of existing websites on the theme (e-Bug, onsexpress.fr, stopHPV) will be carried out, and existing interactive tools and videos dedicated to adolescents will be considered. As tailored interventions are listed in the European Center for Disease Control's Catalog of Vaccine Hesitancy Interventions, adaptation of existing websites is encouraged.

This component firstly includes interventions with Grades 8 & 9 students. These interventions will be based on 3 main tools developed by the PrevHPV SC during the co-construction phase: a serious game, educational videos, and educational tools.

- (i) The serious game: this is a game retracing the day of a teenager. During this day, the adolescent will meet individuals (teachers, friends, parents, school nurses) who will establish a dialogue around HPV-related infections and vaccination. This game will be produced as an application for smartphones and available on a website. It will be usable by adolescents, alone (inside or outside the middle school) or as part of class, but also by parents. This game will be partly co-created with adolescents, parents and teachers during the co-construction phase.
- (ii) Educational videos of 10 to 12 minutes covering 4 themes: pathologies linked to HPV, risk of being infected by HPV, barriers to vaccination, advantages of being vaccinated. These videos will be constructed by health students during the co-construction phase, and will be the subject of a competition to select the best videos. They will be accompanied by explanatory sheets. The jury for this competition will be made up of the project steering committee: 3 videos will be selected. The call for competition will be distributed by the University College of Public Health Teachers, and Health student associations.
- (iii) Educational tools and training intended for biology teachers and school nurses, including existing materials and materials created during the co-construction phase as part of the research (development of an interactive course that they can use with students).

This component also includes information meetings for parents who can come with their teenagers if they wish. These information meetings will be led by GPs, infectious disease specialists and/or gynecologists. Educational support will be co-created by the PrevHPV SC and can be used by speakers at these information meetings. In this context and when possible, we will call on health students integrated into the SeSa systems, particularly for interventions with students.

The implementation of the EMM component with adolescents and their parents will take place on the middle school site between 01/01 and 03/31/2021. The educational tools used during this implementation (serious games, videos and educational tools) will have been previously constructed by the PrevHPV SC in collaboration with the different target populations (adolescents, parents, school staff - co-construction phase).

### • Training of GPs

The training of GPs covers the following three aspects: updated knowledge on HPV infection and its vaccination, short training in the use of motivational interviewing adapted to vaccination, training in the use of decision-aid tool developed by the PrevHPV SC as part of a co-construction process.

- (i) The motivational interview style approach requires respectful and empathetic discussion about vaccination and helps build a strong relationship between parents/teens and the doctor. Parents and teens can freely discuss their concerns and ask questions about vaccination without feeling judged. From this type of doctor/patient relationship, the communication and information delivered by doctors are adapted to the needs of adolescents and parents since they are based on their own representations, concerns and questions. Doctors can identify and target the concerns or misconceptions of adolescents and parents about vaccination. They can thus provide adapted, personalized and therefore non-standardized information.
- (ii) Decision aids are interventions that support patients by making their decisions explicit, providing information about options and associated advantages/disadvantages, and helping to clarify the congruence between decisions and personal values, in concordance with the motivational interview approach. This tool aims to provide in an impartial and objective manner the known and quantified scientific data on HPV (pathologies linked to HPV, risk of being infected, natural history, advantages of being vaccinated, adverse effects linked to vaccination). The tool personalizes the information according to its audience (a teenager will not necessarily have the same concerns as a teenager or even as parents). That is why, the decision aid tool (DA) is co-constructed with adolescents and parents (during the co-construction phase). This tool is also co-constructed with GPs in order to be able to integrate it more easily during the consultation. The International Patient Decision Aid Standards (IPDAS) will be used to design the decision aid (107).

The GP training being considered covers a total duration of four hours. It first includes up-to-date knowledge on HPV infection and vaccination, then an introduction to the use of the technique of motivational interviewing adapted to vaccination, ending with a presentation of the DA tool developed as part of the project to thus facilitate its appropriation. The training is constructed in several short modules and will be accessible online in the form of videos, slideshows, clinical vignettes and interactive modules to offer interview scenarios, follow-ups, questions and answers to patients' questions. To facilitate the adherence of GPs and the reproducibility of this training, we have chosen non-binding and non-face-to-face training, preferring the e-learning type (experience proves that doctors are increasingly resistant to face-to-face training, particularly in the event of geographical distance). To adapt to their different constraints, the training will be accessible at any time and GPs will be able to progress at their own pace. They will also have the opportunity to ask their questions on a discussion forum, moderated by team 2 ([name]) of the PrevHPV SC. The training will be accessible online via the internet and there will be a version adapted for smartphones.

- **Facilitating access to vaccination**

For vaccination in middle schools in the 30 municipalities randomized to groups 1 and 3, the specialty chosen is Gardasil 9® from the MSD Vaccins laboratory which holds the monopoly to date and which is recommended by the HAS for first vaccinations. The choice was oriented towards this specialty because it is the one which offers the greatest protection against different oncogenic HPV serotypes (nonavalent vaccine protects against serotypes 6, 11, 16, 18, 31, 33, 45, 52 and 58), and it is therefore the one mentioned in the current vaccination recommendations (13).

In the 'facilitating access to vaccination' component, only the 1st injection is offered on the middle school premises. The reasons which motivated this choice are as follows:

- (i) In 2018, the HPV VC in France was 29.4% for one dose in girls aged 15 and 23.7% for the complete regimen at 16 years (15), which shows that the main problem is the initiation of vaccination, since 80% of adolescents who initiate vaccination complete it (injection of a 2nd dose).
- (ii) Planning two injections 6 months apart, preceded by the implementation of the EMM component, over a single school year was impossible since health students who participate in the EMM are only available beginning in January. In this context, carrying out the 2nd injection of the vaccine meant that some of the students (mainly those in Grade 9) had to be called back to the middle school even though they were no longer attending school there. This spread of the intervention over 2 school years raised numerous organizational difficulties.

However, measures will be implemented so that adolescents benefit from the complete vaccination schedule:

- mention of the 2nd injection to be carried out in both the written and oral information which will be provided by the doctor from the vaccination center (the date of the next injection will be mentioned orally and in post-vaccination letters) with provision of a prescription for the next injection,
- reminder letter as the 2nd injection approaches.

Once the list of the 30 municipalities benefiting from the 'Facilitation of access to vaccination' intervention has been identified (randomization in groups 1 and 3), contact is made with the DGESCO, the rectorate / diocesan management, the educational establishments, mayors, departmental councils and vaccination centers likely to intervene in educational establishments. A service contract is proposed between the University of Lorraine and the vaccination centers (with compensation for working time) so that they go to the middle schools of the different municipalities in question to vaccinate students whose parents consent to the vaccination.

The project managers of the PrevHPV team, in conjunction with each referent, are responsible for the practical organization of the “Facilitation of Access” intervention on site (date of the half-day(s) of vaccination, order and delivery of vaccines, etc.) and to create a link between middle schools and vaccination centers.

The PrevHPV project managers contact the middle school representatives designated during the “Education, Motivation, Mobilization” intervention and the vaccination center representatives. They agree on the date of vaccination according to the requests and availability of schools and vaccination centers (vaccination can take place over full days or several half-days). They define together the organization to be put in place and the equipment to be made available (various pre-vaccination/post-vaccination letters, familiarization with the equipment available on site: classroom, water point, bed, socket for the computer, table, chairs, emergency kit, catering for the workers if the intervention lasts one day, arrangements for handing over the students, etc.).

The steps of the process are as follows (see flowcharts below):

- (i) In each middle school, the head of the school sends information to parents concerning the presentation of the PrevHPV project (accompanied by the information note specific to the interventions delivered). The middle school referent ensures that information on the vaccination day is disseminated within the school using the most appropriate channels.
- (ii) PrevHPV project managers ensure the distribution of a pre-vaccination letter to schools. A letter containing the main information of the “Facilitation of access” component as well as consent to vaccination is sent to parents through the students, by email and/or made available on the ENT space (e- lyco or Ecole Directe). In this letter, mention is made of the characteristics allowing access to the vaccination offered, carried out by a vaccination center, within the school of the adolescent in question. These characteristics are those presented in the inclusion criteria (see inclusion criteria in the 'Facilitation of access' component, §5.2 Inclusion/non-inclusion criteria). If the adolescent is eligible for vaccination (compliance with all inclusion/non-inclusion criteria), then he or she can benefit from the first injection of the anti-HPV vaccine on the day scheduled at his or her middle school. If in any doubt, parents are encouraged to contact their child's GP or visit the website: <http://vaccination-info-service.fr/>. In the event that parents refuse to vaccinate their child, they can notify in writing directly on the consent document the reason for non-vaccination if they wish.
- (iii) Parents' consent to their child's vaccination is sent to the school's PrevHPV referent. The PrevHPV referent of the middle school, with the possible help of the PrevHPV project manager of the geographical sector concerned, checks that all consents have been correctly completed (in particular the mandatory presence of the signatures of both parents (except in the event of the death of the parents or of child abandonment) and if necessary, they contact the parents to obtain the missing information. Once the consents for vaccination are complete, the middle school referent establishes the list of adolescents who can benefit from free vaccination within the middle school and keep consents to vaccination within the establishment in a lockable cabinet.

- 1162 (iv) The PrevHPV project manager communicates the number of validated vaccination consents to the  
1163 vaccination center in order to estimate the number of vaccines to order and bring for the vaccination  
1164 day. Consents and the list of adolescents eligible for vaccination are kept at the middle school until  
1165 the team from the vaccination center arrives.
- 1166 (v) The logistical organization of vaccination on the site of each middle school is defined by the  
1167 PrevHPV project managers in partnership with the vaccination centers and the schools. The  
1168 PrevHPV project managers complete the poster informing of the date of the day or half-days of  
1169 vaccination and send it to the schools so that they display it (This poster can be published in A5  
1170 format to be given to adolescents whose parents consent to their vaccination in order to remind them  
1171 of the day of vaccination and the importance of bringing the health/vaccination record). Each school  
1172 teaching staff is also informed of the day scheduled for vaccination.
- 1173 (vi) On the day of vaccination, the vaccination center teams made up of at least: a doctor, a nurse ( $\pm$  the  
1174 PrevHPV project manager) go to the middle schools with the vaccines previously received at the  
1175 vaccination center and their emergency equipment in case of anaphylactic shock. The vaccination  
1176 center team sets up in the provided premises. The students are sent to them according to a  
1177 predefined order of passage in groups of two or three individuals in the room made available to the  
1178 vaccination centers in accordance with the provisions previously established according to the  
1179 organization of each establishment.
- 1180 (vii) The doctor of the vaccination center verifies that the adolescent meets the inclusion criteria of the  
1181 protocol, vaccinates and completes the health record.
- 1182 (viii) On the nominative list of consents to vaccination, the vaccination center nurse or the PrevHPV  
1183 project manager records whether the vaccination is carried out or not on a paper list.
- 1184 (ix) All students who have received an injection remain under the supervision of the vaccination center  
1185 doctor for 15 to 20 minutes before returning to class. During the post-vaccination surveillance period,  
1186 a satisfaction questionnaire is given to adolescents who complete it on site. The nurse gives the  
1187 student a post-vaccination letter in a sealed envelope intended for his or her parents in which it will  
1188 be mentioned whether or not the vaccination has been carried out and the future injection(s) to be  
1189 planned. (for parents who have consented but whose adolescent has not been vaccinated, a non-  
1190 vaccination letter is sent to them). Subject to the acceptance of the parents of the vaccinated child  
1191 (information formalized in the vaccination consents), a letter addressed to the adolescent's treating  
1192 physician is sent directly either by the vaccination center or by the PrevHPV project manager of the  
1193 geographical area concerned. In addition, parents can give a note to their community pharmacist if  
1194 they wish to complete the pharmaceutical file.

In the post-vaccination information letters to parents and treating doctors, it will be specified that a second or even a third injection is necessary for the vaccination to be complete as well as the period at which it should be carried out. The prescription for the following injection will be made by the doctor at the vaccination center and provided with the other documents for parents.

At the end of the vaccination day, the satisfaction survey will be made available to the professionals of the school involved in the intervention in order to measure the possible incidence during the adolescents' school hours. The completed satisfaction questionnaires will be collected by the middle school referent.

Overall assessment of the vaccination day:

- Number of days organized
- Number of vaccinations requested
- Number of complete vaccination consents,
- Number of incomplete vaccination consents
- Number of vaccinations carried out
- Number and list of adverse effects
- List of technical or organizational problems
- Number of satisfaction surveys and results, collected from middle school students and professionals at the school.

(x) In the weeks following the vaccination day, at the initiative of the PrevHPV project manager, a meeting will be proposed with the referent and the director or principal of the school to summarize all of the EMM and Facilitation of access interventions. The summary will also be communicated to the vaccination center. The project manager will collect the satisfaction questionnaires from school teaching staff that same day from the middle school referent.

(xi) Depending on the age of the vaccinated adolescents, reminders are sent by email or postal mail to the adolescents' parents and the adolescents' treating physicians to inform of the need to complete the complete vaccination schedule:

- at 6 months for adolescents under 15 years old
- at 2 and 6 months for adolescents over 15 years old

• **Distribution of the implementation of interventions by The PrevHPV SC team**

The 'EMM' and 'Facilitation of access to vaccination' components will be implemented in the field by teams 1, 3, 4, and 5 who will distribute the 90 participating municipalities among themselves according to their geographical proximity.

The 'Training of GPs' component will be implemented in the field by team 2, with the help of team 3 (see part 15).

